## Methods and Analysis

### Study Design

A multi-site, cluster RCT with a qualitative component will be implemented (Figure 1). Using a minimization randomization procedure over size of GP clinic (<4 GPs or ≥4) and site (NSW or VIC), the participating GP clinics within the two Australian States (NSW and VIC) will be allocated to one of two arms:

Surveillance as Usual (SaU), representing current practice, orASD surveillance pathway (ASP), which will implement the “enhanced surveillance” protocol.

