### Phase 1 - GP Clinic Visit

Prior to commencing the study, GPs and PNs will receive training on the study procedure and use of the study iPad and weblink, and, for those in the ASP group, the study screening tools. Clinic reception staff will also receive training on the study procedure and participant recruitment. Potential participants will be identified by reception staff when the child presents for their GP appointment, by staff checking the child's age in the patient record. Reception staff will offer the child's parent/caregiver information on the study in the form of a study flyer. Clinics will also have study posters with the same information on display. Parents/caregivers who would like to participate in the study will be asked to complete the participant information and consent form and demographic questions on the study iPad (or via their own mobile device), with those in the ASP group also completing developmental screening questionnaires. Once the parent/caregiver completes the developmental screening questionnaires and submits the response using the weblink, the GP receives the results via email or the Salesforce platform so that this information is available to the GP at the point of care during the consultation.

Table 1 summarizes clinical and behavioral measures and assessments for both ASP and SaU pathways. Measures will be taken at various points in the trial to allow appropriate comparisons between the groups (see Figure 1 and Table 1). Client-facing documents such as the information sheet, consent form, and screening questionnaires have been translated into Arabic, Chinese (Mandarin), and Vietnamese, the most common languages spoken by culturally and linguistically diverse (CALD) families in our study locations.

**Table 1 T1:** Study Flow Chart.

**Time points**	**Age (months)**	**Location**		**Groups and tools**		
1	18–24		**Autism surveillance pathway**		**Surveillance as usual**	
			Service data		Service data	
		Waiting Room	Consent Demographics LTSAE; PEDS Q-CHAT-10		Consent Demographics	
		Doctor's Office	SACS Online (GP completes)		Brief online form to inform research team of high ASD risk, type of concern, screening method used, and referrals and recommendation provided	
			**Developmental concerns (any)**	**No concerns**		
		Waiting Room	ASQ:SE (option to complete at home)	–	–	
			**High ASD risk**	**Low ASD risk 10% complete**	**High ASD risk**	**Low ASD risk 10% complete**

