### Procedure

Parents/caregivers of children in both the ASP and SaU arms who are identified as having a “high likelihood” for autism at 18- or 24-months will be invited by the researchers for a developmental assessment when the child is ~24 months of age. Additionally, a randomly selected 10% of screen negatives from both groups will also be invited to complete this same assessment at ~24 months of age. These assessments will be undertaken by trained researchers who have achieved research-reliable coding on the ADOS-2 as well as having trained on the other measures described below. Parents/caregivers will complete a more detailed general and demographic questionnaire in addition to the following assessments: The ADOS-2 and ADI-R, together with the developmental assessment, and clinical judgement, will be used to determine whether the child meets a DSM-5 diagnosis of ASD.

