### Analytical Plan

#### Sample Size

The total sample size of children recruited into the study will be 2,400 children across the two sites, which will provide adequate statistical power to address the study hypotheses. This sample will enable us to achieve 80% power to detect a difference between the two group means of 0.0935 standard deviations (SD) using a significance level of 0.05. In analyses comparing the smallest anticipated subgroups (as small as 20% of the original group sizes), a mean difference of 0.21 standard deviations will be detectable retaining the same power and significance levels. For the qualitative component of the study, it is envisaged that approximately twenty participants (GPs and PNs) will be enough to obtain thematic data saturation.

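### The subgroup sensitivity of 0.21 SD does not follow from 20% of 2,400 children, and the 24-month screen-negative sample lies below the stated 20% floor

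*Protocol article*

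**What the plan says.** The Sample Size section fixes enrolment: "The total sample size of children recruited into the study will be 2,400 children across the two sites". It claims 80% power for a difference in means of 0.0935 SD, "using a significance level of 0.05". For the smallest anticipated subgroups, described as "as small as 20% of the original group sizes", it adds that "a mean difference of 0.21 standard deviations will be detectable retaining the same power and significance levels". It does not name those subgroups.

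Under Study Design, clinics "will be allocated to one of two arms"; no allocation ratio is given.

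Under Phase 2, Procedure, the 24-month assessment is offered to children flagged as high likelihood in either arm and to "a randomly selected 10% of screen negatives from both groups". Table 1 shows the second group as its own column in each arm, headed "Low ASD risk 10% complete". The text introducing Table 1 says that measures are taken so that the groups can be compared.

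**The concern.** The subgroup sentence is the only statement of sensitivity a reader has for any analysis on less than the full sample. It is doubtful for two reasons. First, the figure can be recomputed from the article's own numbers and does not come out. Second, a floor of 20% for the smallest subgroup sits beside a design that creates one of at most 10%.

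The ADOS-2, ADI-R, MSEL, VABS-3, SEQ and ITSP are collected only from children assessed at 24 months. If arms are compared on these measures within flagged or screen-negative children, a null result read against 0.21 SD would look more informative than it is.

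**Working it through.** **Inputs.** From the article: 2,400 children, two arms, 80% power, alpha 0.05, a subgroup share of 20%, a 10% sample of screen negatives, and about 60 clinics of about 40 children. Assumed: equal arms (1,200 each), a two-sided test with one-sided as a check, independent children, and full attendance.

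**Formula.** Detectable difference in SD units = (z for alpha + z for power) × √(1/n1 + 1/n2). The multiplier is 1.960 + 0.842 = 2.802 two-sided, or 1.645 + 0.842 = 2.487 one-sided.

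**Step 1: try to reproduce the stated figures.**
- Full sample, 1,200 per arm: 2.802 × √(2/1200) = 0.114 SD (one-sided 0.102). Stated: 0.0935. Power for 0.0935 SD is 63% (one-sided 74%). Required: 2 × (2.802/0.0935)² ≈ 1,796 per arm (one-sided 1,415).
- 20% subgroup, 240 per arm: 2.802 × √(2/240) = 0.256 SD (one-sided 0.227). Stated: 0.21. Power for 0.21 SD is 63% (one-sided 74%). Required: 2 × (2.802/0.21)² ≈ 356 per arm (one-sided 281).
- Unequal arms do not help: a 40:60 split of 2,400 gives 0.117 SD and a 30:70 split gives 0.125 SD.
- The two stated figures agree with each other, since 0.0935 × √5 = 0.209. Both fit 1,800 per arm (0.0934 SD, and 0.2088 SD at 360 per arm), but not 1,200.

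**Step 2: the screen-negative sample.** If a proportion f of an arm is flagged, this sample is 0.10 × (1 − f) × 1,200 = 120 × (1 − f). It cannot exceed 120 per arm, so the detectable difference is at least 2.802 × √(2/120) = 0.362 SD. Power for 0.21 SD at 120 per arm is 37%. This step needs no flag rate.

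**Step 3: groups that depend on the flag rate.** The article gives none for either arm. Its nearest figure, up to 30% at developmental risk (Introduction), is not an autism flag rate. The share assessed is f + 0.10 × (1 − f). With the same assumed f in both arms:

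| Assumed f | Flagged per arm | SD | Screen-negative sample per arm | SD | All assessed per arm | SD |
|---|---|---|---|---|---|---|
| 5% | 60 | 0.511 | 114 | 0.371 | 174 | 0.300 |
| 10% | 120 | 0.362 | 108 | 0.381 | 228 | 0.262 |
| 11.1% | 133 | 0.343 | 107 | 0.384 | 240 | 0.256 |
| 20% | 240 | 0.256 | 96 | 0.404 | 336 | 0.216 |
| 30% | 360 | 0.209 | 84 | 0.432 | 444 | 0.188 |

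All assessed children together reach 20% of an arm at f = 0.1/0.9 = 11.1%, and reach 0.21 SD at about 22% flagged: (356/1200 − 0.1)/0.9. Flagged children alone reach 0.21 SD at about 30% (356/1200).

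With unequal assumed rates of 5% in SaU and 15% in ASP, flagged children number 60 and 180: 2.802 × √(1/60 + 1/180) = 0.42 SD.

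**Step 4: clustering.** The design effect is 1 + (m − 1) × ICC. At an assumed ICC of 0.02, the full sample (m = 40) has a design effect of 1.78, so 0.114 becomes 0.153 SD. The 20% subgroup (m = 8) has 1.14, so 0.256 becomes 0.273 SD. Non-attendance would worsen the 24-month figures further.

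**The case against.** The strongest reply is that the 20% is never tied to the 24-month assessment. It could refer to baseline subgroups of all enrolled children, for whom the SRS-2 is collected at 30 months. The listed outcomes are uptake, correct identification, referral and service use, and the first two are to be analysed as risk differences. The article lists no between-arm comparison of mean scores among screen negatives, and the 10% sample may serve only to verify negative screens.

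Much of this stands. A reader might infer that the whole 24-month data set is under 20% of an arm, so that 0.21 SD is out of reach for every 24-month comparison. The article does not support that. It gives no flag rate, the ASP rule for high likelihood is broad (either of two autism tools, or a combination of general ones), and the assessed share passes 20% once 11.1% are flagged. At 30% flagged in both arms, all assessed children together would do better than 0.21 SD. A reader might also infer that the figures were computed for 3,600 children; the arithmetic fits, but the article does not say so.

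The reply does not rescue the stated figures. Whatever the subgroups are, 240 per arm does not give 0.21 SD. A floor for the smallest anticipated subgroups also sits badly with a group that Table 1 displays separately and that cannot exceed 10% of an arm.

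**Conclusion.** The point holds in limited form, in three parts of different strength.

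- **Firm:** neither 0.0935 nor 0.21 SD follows from 2,400 children. The corresponding values are about 0.114 and 0.256 SD, given equal arms and a two-sided test without clustering. A one-sided test (0.102 and 0.227) does not recover the stated figures, and unequal arms or clustering widen the gap.
- **Firm on size, conditional on use:** the screen-negative sample is at most half the stated floor and supports at best about 0.36 SD. This matters to the extent that arms are compared within it.
- **Conditional:** flagged groups are below 20% of an arm whenever fewer than 20% are flagged. How far below cannot be settled from the article.

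The 30-month SRS-2 covers all children and is not limited by the 24-month selection, though it is subject to the full-sample correction. The paragraph should be corrected; the design need not be.

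**What to change.** Rewrite the quantitative part of the Sample Size paragraph on one basis:

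- Replace both figures together: about 0.114 SD for 1,200 per arm and 0.256 SD at 20%, before clustering. Changing only the subgroup figure would leave the paragraph on two incompatible bases.
- State the allocation ratio and whether the test is one- or two-sided.
- Name the subgroups that the 20% refers to.
- Add the screen-negative sample (at most 120 per arm, about 0.36 SD at best) and the flagged groups over a stated range of flag rates for each arm.
- Inflate each figure by a design effect for the number of children per clinic in that analysis, with the assumed ICC stated, and allow for non-attendance at 24 months.

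The cost is one paragraph of restated figures. Enrolment and procedures do not change. The downside is that the stated sensitivity becomes less favourable.

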### Statistical Analysis

#### Quantitative Analysis

The entire raw dataset will be provided to an independent biostatistician, along with the study protocol and the pre-specified statistical analysis plan, who will conduct an independent analysis of the raw data. Details of this independent statistical analysis, as well as the name and academic institution of the independent statistician and whether compensation or funding was received for conducting the analyses, will be included in the publication of the results of the study.

Descriptive statistics for outcome measures (percentage, mean, and SD) and psychometric properties of the measures (reliability, Cronbach's α) will be reported. Descriptive statistics for all parental socio-demographic will also be presented, with the expectation of no group differences. We will compare the differences between the control arm (SaU) and the intervention arm (ASP) for the following primary outcomes:

(1a). the uptake of autism developmental surveillance as indicated by the proportion of children who participated in the program;(1b). the proportion of children correctly identified by the GPs as being at “high likelihood” of autism, and later confirmed as having ASD through the “gold standard” assessment.(2) the proportion of children in both groups who received referrals following identification of developmental concerns;(3) the access and utilization of child health and developmental services will be ascertained based on the uptake of recommendations as assessed at the 30-month follow up.

analysis to determine the overall effectiveness of the “enhanced” autism surveillance pathway will involve comparison between the two groups, adjusting for potential confounders which are significantly different between clusters or strongly associated with the outcome variable, such as gender, maternal education, and socioeconomic status. Outcome group differences in the uptake of developmental surveillance, completion of surveillance tools and accurate identification of children at high likelihood of autism and diagnosed with ASD will be investigated using risk difference (RD) with 95% confidence interval (CI) and, where indicated, kappa coefficients. We will use generalized estimating equations (GEE) modeling to identify if there are factors other than the intervention that may also explain differences between the two arms. The intervention will be considered as a fixed effect and cluster assignment as a random effect, to account for group membership. Such modeling techniques adjust for clustering and also allow the inclusion of both cluster- and individual-level covariates. Statistical analysis will be carried out using IBM SPSS Statistics version 26 (66), Mplus 7.1 (67), and R v4.0.1 (68).

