## Aims and Objectives

The overall objective of the project is to develop and evaluate a potentially sustainable approach to ASD detection within a developmental surveillance framework, in children aged 18–24 months using opportunistic GP clinic visits in the primary care setting. Specifically, this project will aim to examine whether, compared to Surveillance as Usual (SaU), an ASD Surveillance Pathway (ASP) will be associated with: (a) improved uptake and completion of developmental and autism surveillance; and (b) increased accuracy in identifying children at “high likelihood” of autism and related conditions, such as developmental and/or language delay. Secondary outcomes to be investigated include whether the ASD surveillance pathway will increase parental/caregiver engagement, health literacy, and satisfaction in accordance with the NAG, and increase GP awareness and utilization of developmental and autism surveillance tools and resources.

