### Measures

#### Autism Surveillance Pathway (ASP)

The parent completed developmental surveillance instruments are listed below.

“Learn The Signs Act Early” (LTSAE) developmental checks as recommended by the Centre for Disease Control (41) are used to monitor children's early development in the domains of social and emotional, language/communication, cognitive (learning, thinking, problem-solving), and movement/physical development. These developmental milestone checklists are available for children aged 2 months to 5 years, and the checklists for 18–23 and 24–29 months are included in this study. The aim of the LTSAE used by the NSW Health as part of the developmental surveillance program is to engage families and encourage parents/caregivers and health service providers to learn/monitor the signs of healthy development.

The Parents' Evaluation of Developmental Status (PEDS) (42) is designed for children from birth to 8 years of age and consists of ten questions asking parents/caregivers about concerns they have in domains including global/cognitive, expressive language and articulation, receptive language, fine and gross motor, behavior, self-help, socialization, and academic. It is widely used in Australia and is the first-line developmental surveillance tool used in state-based programs in most states in Australia and internationally. Screening test characteristics are over 70% for sensitivity and specificity for developmental concerns.

The Quantitative Checklist for Autism in Toddlers-10 item (Q-CHAT-10) is an ASD-specific ten-item tool to aid the decision making for primary care professionals about whether to refer a child for a full diagnostic assessment for ASD. The ten most accurate items from the original Quantitative Checklist for Autism in Toddlers (Q-CHAT) (43) were identified and included in this shortened version. Using a cut-off point of three, the Q-CHAT-10 has sensitivity of 0.91, specificity of 0.89, positive predictive value (PPV) of 0.58, and internal consistency of 0.85, when used in a *clinical population*; its utility when used in community-based samples has not been reported (44).

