The Ages and Stages Questionnaire: Social Emotional scale (ASQ:SE) (45) is a screening tool focusing on the social and emotional behavior of children aged 6- to 60-months. This study uses the *18- and 24-month questionnaires*. Parents are asked a series of questions regarding their child's self-regulation, communication, autonomy, compliance, adaptive functioning, affect, and interaction with people. The ASQ (46) and the ASQ:SE have sound psychometric properties and the ASQ/ASQ-SE is the recommended developmental surveillance and health monitoring program in all Australian States with the exception of Victoria [where the Brigance Screens is used in its place (47)] for identification of developmental problems. The measure has been shown to have good reliability as a developmental screener globally with Cronbach's alpha of 0.79 for the total score and 0.61–0.74 for all the domains indicating acceptable reliability (48).

GP/PN completed autism developmental surveillance instrument:

The Social Attention and Communication Surveillance – Online (SACS Online) tool (34–37) is a professional observational tool intended for use in 11- to 30-month-old children, with the 18- and 24-month versions in use for this current study. Originally designed for use by maternal and child health nurses it is also suitable for use by other primary health professionals. The tool consists of five “key” behavioral items per age group plus additional items, with professionals asked to note whether the child is displaying typical or atypical behavior for each item. Where a child is noted to have atypical behavior for three of the five “key” items, it is recommended that they be referred for further assessment. Study results have indicated that the SACS tool and its revised version have high sensitivity (82–84%), specificity (99–99.8%), PPV for autism (81–83%; and 100% for *any* language/developmental delay or condition), and negative predictive value (99%), making it highly suitable for use in primary- and community-health and early childhood settings (34, 36). In the current study, GPs and PNs will be provided with access to the training modules in the use of the SACS Online tool via their online study portal, which they will complete prior to commencing child assessments.

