### Procedures

#### Autism Surveillance Pathway (ASP)

Parents/caregivers in the ASP arm will complete electronic versions of a participant information and consent form, a brief demographic questionnaire, in addition to the LTSAE, PEDS, and Q-CHAT-10 in the GP clinic waiting room. REDCap (NSW site) and Salesforce (VIC) will be used to manage the completion of these forms and questionnaires. An embedded algorithm on the REDCap and Salesforce platforms will score the parent responses to identify children as having developmental risk and/or high likelihood for autism, and this information from the initial assessments will be passed on automatically to the child's GP (and PN if applicable). During the consultation, the GP (or PN) will also complete the SACS Online using the Salesforce platform at both NSW and VIC sites. The ASQ:SE will be completed by parents/caregivers of children identified as having any developmental concern following completion of the LTSAE, PEDS, Q-CHAT-10, and/or SACS Online. Children will be determined as having a “high likelihood” for ASD if they: (a) are identified as “high likelihood” for autism by either the Q-CHAT-10 *or* the SACS Online assessment (regardless of the outcome of the other tools); or (b) are identified as at developmental risk by LTSAE and/or PEDS *and* ASQ:SE (but were found not at high likelihood for autism by Q-CHAT-10 and SACS Online).

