### Phase 3 – 30-Month Assessment Protocol

Parents/caregivers of all children recruited to both the ASP and SaU arms of the study will complete the preschool version of the Social Responsiveness Scale, Second Edition (SRS-2)(60, 61) when their child is ~30 months of age. The SRS-2 is an autism screening tool that asks parents/caregivers to rate their child's traits of autism, as seen in a naturalistic setting, on a quantitative scale. The total score provides an indication of the extent of social differences. The SRS has good internal consistency (α = 0.93) and good test-retest reliability in preschoolers (intra-class correlation = 0.74) (61, 62).

Parents/caregivers of children identified with a developmental condition from both arms will also complete a semi-structured questionnaire to evaluate the uptake of recommendations, experience of assessment/service use, disability supports, and early intervention received and parental satisfaction with the health and disability services. This will facilitate comparison between those in the ASP arm who received the assessments and recommendations using the NAG and those in the SaU arm who received routine care.

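### Aim (b) claims increased accuracy, but no listed outcome counts children who are flagged and then not confirmed to have ASD

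*Protocol article*

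**What the plan says.** - **Aim.** Aims and Objectives, aim (b), asks whether the ASP is associated with "increased accuracy in identifying children at" high likelihood of autism and of related conditions such as developmental or language delay.
- **Flag rule.** Procedures, Autism Surveillance Pathway, flags a child who is positive on the Q-CHAT-10 or on SACS Online, "regardless of the outcome of the other tools". A further route flags children at risk on LTSAE and/or PEDS and also on ASQ:SE, "but were found not at high likelihood for autism by Q-CHAT-10 and SACS Online".
- **Tool accuracy.** Measures, Autism Surveillance Pathway, states that "the Q-CHAT-10 has sensitivity of 0.91, specificity of 0.89, positive predictive value (PPV) of 0.58" in a clinical population, and that "its utility when used in community-based samples has not been reported". For SACS it gives sensitivity 82–84% and specificity 99–99.8%.
- **Outcomes.** Quantitative Analysis lists (1a) uptake; (1b) "the proportion of children correctly identified by the GPs" and later confirmed by the reference assessment; (2) referrals; and (3) service use. The denominator of (1b) is not stated. Accurate identification is to be analysed by risk difference and, where indicated, kappa.
- **Reference assessment.** The Phase 2 Procedure invites all flagged children in both arms, and a random 10% of screen negatives, to the same assessment at about 24 months.
- **30 months.** Phase 3 gives the SRS-2 to every recruited family. It then says: "Parents/caregivers of children identified with a developmental condition from both arms will also complete a semi-structured questionnaire". Table 1 appears to place that questionnaire under the High ASD risk columns of both arms.

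**The concern.** Accuracy has two sides: finding affected children and not flagging unaffected ones. Outcome (1b) sees only the first. Taken per recruited child, which is its natural reading, it can only rise or stay level as more children are flagged. Outcome (2) does not correct this, because a referral after a mistaken flag counts the same as one after a correct flag.

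The ASP flag rule is built to be inclusive, and the control arm has no comparable rule. A favourable (1b) could therefore reflect more flagging rather than better discrimination. The Discussion looks towards a programme that can be scaled across Australia. A decision of that kind needs the number of families flagged without a confirmed condition as well as the number of cases found.

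**Working it through.** **Inputs from the document.** Q-CHAT-10 sensitivity 0.91, specificity 0.89, PPV 0.58; SACS sensitivity 0.82–0.84, specificity 0.99–0.998; 2,400 children in all.

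**Assumptions.** 1,200 children per arm (equal split), and autism prevalence p of 1–3% among recruited children. The document gives no prevalence.

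**1. The quoted PPV.** Solving PPV = 0.91p / (0.91p + 0.11(1 − p)) for PPV = 0.58:

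p = 0.58 × 0.11 / (0.91 × 0.42 + 0.58 × 0.11) = 0.0638 / 0.4460 = 0.143.

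So 0.58 belongs to a sample with about 14% prevalence. It would not carry over to toddlers attending a GP for any reason.

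**2. Ceiling on specificity.** A child without ASD escapes a flag only by being negative on every route. Combined specificity is therefore at most that of the Q-CHAT-10. This needs no independence assumption.

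**3. Q-CHAT-10 alone, per 1,200 ASP children, if 0.91/0.89 held.** Flagged without ASD = 1,200 × (1 − p) × 0.11; confirmed = 1,200 × p × 0.91.

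| p | Confirmed | Flagged without ASD | PPV |
|---|---|---|---|
| 1% | 10.9 | 130.7 | 7.7% |
| 2% | 21.8 | 129.4 | 14.4% |
| 3% | 32.8 | 128.0 | 20.4% |

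**4. Either tool positive, p = 2%, errors assumed independent.** Specificity = 0.89 × 0.99 to 0.89 × 0.998 = 0.881 to 0.888. Flagged without ASD = 1,176 × 0.119 to 1,176 × 0.112, about 140 to 131 (from unrounded values). Confirmed = 24 × (1 − 0.09 × 0.18) to 24 × (1 − 0.09 × 0.16), about 23.6 to 23.7. PPV is about 14–15%. The third route can only add to the flags.

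**5. What (1b) would register.** At p = 2%, the stated SACS figures alone would give about 20 confirmed children (24 × 0.82–0.84) and 2–12 flagged without ASD (1,176 × 0.002–0.01). Going from that to the either-tool rule moves (1b) per recruited child from about 20/1,200 = 1.7% to 24/1,200 = 2.0%. The proportion flagged without ASD moves from at most 12/1,200 = 1% to about 131–140 of 1,200, or 11–12%. Only the first change appears in a listed outcome. The two tools' figures come from different kinds of sample, so this illustrates what the outcome can see. It does not compare the tools.

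**6. Dependence on 0.89.** With sensitivity held at 0.91, unconfirmed flags equal confirmed ones when 1 − specificity = 0.91p/(1 − p): 0.009 at 1%, 0.019 at 2% and 0.028 at 3%. Community specificity would have to reach about 0.97–0.99 before unconfirmed flags stopped being the majority.

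**7. The 30-month questionnaire.** The Phase 3 text selects on an identified developmental condition, while Table 1 appears to select on the GP-visit flag. The two differ for children who were flagged and then found to have no condition.

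**The case against.** **Data are collected.** The strongest reply is that the 24-month assessments of all flagged children and of 10% of screen negatives allow PPV, specificity and sensitivity to be estimated. Kappa, where used, would fall as mistaken flags rise. Outcome (2) picks up referral load, though unsplit, and the parent interviews can include families of wrongly flagged children. All of this stands. A reader might infer that false flags cannot be, or will not be, reported; the document does not support that. The gap is that no listed outcome counts them.

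**Left to the analysis plan.** Derived accuracy statistics may be specified in the plan that is not shown. That is fair for methods. But the article itself lists the primary outcomes, and the list is one-sided relative to aim (b).

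**Denominator.** If (1b) were taken over flagged children it would be the PPV, and more flagging could lower it. The article does not say so, and the hypothesis speaks of a proportion of children correctly identified. The ambiguity is itself a reason to state the denominator.

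**Size.** The 0.89 comes from a clinical population, and a child without ASD is not necessarily wrongly flagged, because aim (b) includes related conditions. Both limits stand.

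**Follow-up.** A reader might also infer that wrongly flagged families are dropped at 30 months. They are not: every family receives the SRS-2. Only the semi-structured questionnaire is in doubt, and the layout of Table 1 was machine-read.

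**Conclusion.** The point holds in a limited form. Outcome (1b) on its own cannot support a claim of increased accuracy, because on a per-child reading it carries no penalty for flags that are not confirmed, and no other listed outcome supplies one. The ceiling on ASP specificity follows from the flag rule alone.

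The size, about 130 of 1,200 ASP children flagged without ASD by the Q-CHAT-10 alone with a PPV of about 8–20%, is illustrative. It rests on the clinical-sample accuracy carrying over, on equal arms and on 1–3% prevalence. It is an upper limit for children with no condition at all flagged by that tool, since some of the 130 would have a developmental or language delay. The document names no harm to families, so this is a gap in measuring accuracy and not evidence of harm. It is also no judgement on which flag rule is right. The mismatch between Phase 3 and Table 1 is a separate and smaller matter of clarification.

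**What to change.** 1. State the denominator of (1b) as all recruited children.
2. Beside (1b), report by arm and per recruited child the proportion flagged at the GP visit and found at 24 months to have (i) no ASD and (ii) no developmental condition. Add the PPV among flagged children assessed, and show flagged children who did not attend as a separate count.
3. State that any conclusion of increased accuracy rests on these figures together with (1b).
4. Reconcile the Phase 3 text with Table 1 on who receives the semi-structured questionnaire.

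Items 1 to 3 use assessments already planned and need no new visits; item 4 is a wording change. The downside is that the headline result may look less favourable once unconfirmed flags stand next to confirmed ones.
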